| MEDEX-I               | Meditation Experiences Interview                           |
| MSAS                  | Mindfulness Skill Acquisition Scale                        |
| MSPSS                 | Multidimensional Scale of Perceived Social Support         |
| NCCAM                 | National Center for Complementary and Alternative Medicine |
| NIH                   | National Institutes of Health                              |
| OM                    | Open Monitoring                                            |
| PANAS                 | Positive and Negative Affect Schedule                      |
| PSG                   | polysomnography                                            |
| RA                    | Research Assistant                                         |
| SAE                   | Serious Adverse Event                                      |
| SART                  | Sustained Attention to Response Task                       |
| SCID                  | Structured Clinical Interview for DSM-IV                   |
| SCO                   | Self-Compassion Scale                                      |
| SLT                   | Sleep Latency test                                         |
| SPS                   | Spiritual Perspectives Scale                               |
| SRT                   | Self-referencing Task                                      |
| TFI                   | Therapeutic Factors Inventory                              |

|            |                                |
|------------|--------------------------------|
| WAI | The Working Alliance Inventory |
| WBS | Wellbeing Scale                |

## Protocol Summary

| Full Title                      | Dismantling Mindfulness: Contributions of Attention vs. Acceptance                                                                                                                                                                                                                                                                                                             |
|----------------------------------------|--------------------------------------------------------------------------------------------------------------------------------------------------------------------------------------------------------------------------------------------------------------------------------------------------------------------------------------------------------------------------------|
| Short Title                     | Dismantling Mindfulness:                                                                                                                                                                                                                                                                                                                                                       |
| Conducted By                    | Department of Psychiatry and Human Behavior, Brown University                                                                                                                                                                                                                                                                                                                  |
| Principal Investigator          | [name]                                                                                                                                                                                                                                                                                                                                                             |
| Sample Size                     | 105                                                                                                                                                                                                                                                                                                                                                                            |
| Study Population                | Individuals with mild-severe affective disturbances (depression)                                                                                                                                                                                                                                                                                                               |
| Accrual Period                  | 3 years                                                                                                                                                                                                                                                                                                                                                                        |
| Study Design                    | Three-armed clinical trial. Groups of participants will be randomly allocated into either a(n) i.) focused awareness (FA), ii.) open monitoring (FA), or iii.) traditional MBCT arm.                                                                                                                                                                                           |
| Study Duration                  | Career development award: 5 years, 07/01/2011- 06/30/2016
Data collection: 3 years
6 months per participant: 8 week intervention and 3 month follow-up.                                                                                                                                                                                                                  |
| Intervention Description        | One of three types of meditation: 1) focused awareness 2) open monitoring , or 3) Mindfulness-Based Cognitive Therapy (both practices combined)

Intervention is group format, 2.5 hours once a week for 8 weeks.                                                                                                                                                        |
| Primary Objective of this Award | The purpose of the research described in this Mentored Patient-Oriented Research Career Development Award (K23) is to facilitate my becoming an independent investigator.

Study the Effects of Different Types of Meditation on Depression and Negative Affect                                                                                                          |
| Primary Research Objective      | 
 
• To create two separate treatment modules with specific criteria for the two core components and practices of attention training/focused awareness (FA) and acceptance/open monitoring (OM); establish feasibility and acceptability
 
• To establish the effect sizes of FA and OM vs MBCT in a controlled trial in
 
 |

|                                      |                                                                                                                                                                                                                                                                                                                                                                                                                                                                      |
|--------------------------------------|----------------------------------------------------------------------------------------------------------------------------------------------------------------------------------------------------------------------------------------------------------------------------------------------------------------------------------------------------------------------------------------------------------------------------------------------------------------------|
|                                      | individuals with mild-severe depression and persistent negative affect.                                                                                                                                                                                                                                                                                                                                                                                              |
| Secondary Research Objectives | 
 
• To assess and compare the effects of FA, OM, and MBCT on subjective and objective measures of 3 domains of PFC functioning: 1) attention, 2) emotional reactivity/regulation and 3) wakefulness.
 
• To determine which neurobehavioral processes (attention, emotion regulation, wakefulness) drive the clinical benefits of mindfulness training, independent of treatment allocation or practice type.
 
 |
| Endpoints                     | 1)Depression/Negative Affect:
2)Attention:
3) Emotional Reactivity/Regulation:
4) Wakefulness/Sleepiness:                                                                                                                                                                                                                                                                                                                                                   |
|                                      |                                                                                                                                                                                                                                                                                                                                                                                                                                                                      |

## 2. INTRODUCTION

### 2.1 Patient Oriented Mentored Career Development Award

The research project described in this protocol is part of Career Development Award. The primary aim of the research is to provide the PI with training in conducting clinical intervention research, and to provide pilot data for a larger trial (R01). Thus the primary goal of this award (training) is a central part of the design considerations for the research study. It should also be noted that \$25,000 per year is available for research, which covers the cost of one paid research assistant. Thus, feasibility should also take into account the limited budget.

### 2.2 Specific Aims

**The primary aim of this K23 proposal is to provide hands-on training to facilitate my becoming an independent investigator in patient-oriented meditation research with an emphasis in mechanisms of action.**

Meditation, particularly mindfulness meditation, is one of the most popular Complementary and Alternative Medicine (CAM) therapies for alleviating mild-severe emotional stress, depression and anxiety and promoting wellbeing (NCCAM, 2009a; Schroevers & Brandsma, 2009). However, despite the widespread application and proliferation, numerous methodological limitations in available research preclude definitive claims about clinical effectiveness or mechanism of action (Davidson, in press; Ludwig & Kabat-Zinn, 2008; Ospina et al., 2007). At present, the largest barrier to meditation research in general, and mindfulness research in particular, is the failure to delineate meditation based-treatment packages into their most basic components and practices (Davidson, 2010)(Davidson, in press; Ospina et al., 2007).

Mindfulness has been defined as being comprised of two components: 1) attention training component and 2) an affective orientation of acceptance/non-reactivity (Bishop et al., 2004; Rapgay & Bystrisky, 2009). These two components correspond to two separate meditation practices, focused awareness (FA) and open monitoring (OM), respectively (Davidson, in press; Lutz et al., 2008; Rapgay & Bystrisky, 2009). FA and OM practices are thought to have different neural underpinnings and different cognitive affective and behavioral consequences (Lutz et al., 2008; Rapgay & Bystrisky, 2009). However, there is much debate in both traditional Buddhist and western science about the relative importance of each component for clinical benefit for the alleviation of affective disturbance (Davidson, in press; Rapgay & Bystrisky, 2009; Shankman, 2008). For example, the role of attention training (FA), which is foundational to nearly all forms and traditions of meditation practice, is increasingly diminished in favor of acceptance in the new wave of mindfulness therapies (Rapgay & Bystrisky, 2009). Since the respective contributions of each component have never been assessed, the recent trend of decreasing the proportion of attention training in mindfulness-based therapies may be eliminating an indispensable ingredient that is key to treatment success. Alternatively, it is possible that programs that demand hours of FA training are misinformed and could allocate treatment time to more efficacious techniques or approaches.

Mindfulness-Based Stress Reduction (MBSR) and its close cousin Mindfulness-Based Cognitive Therapy (MBCT) dedicate approximately half of treatment time to attention training/FA and the other half to acceptance/OM (Santorelli & Kabat-Zinn, 2003; [name], Williams et al., 2002). However, because these two components and practices are delivered in an

integrated format it is difficult to assess their individual contributions to treatment success or their different mechanisms of action. Therefore, the primary goal of the proposed research is to dismantle MBCT into the separate core components/practices of the attention/FA training and acceptance/OM training and to assess each component and practice independently in a controlled trial in 105 individuals with mild-severe affective disturbances.

It has been proposed that the therapeutic effects of mindfulness meditation are mediated by strengthening prefrontal attention and emotion regulation systems (Chambers et al., 2009; Creswell et al., 2007; Davidson & Lutz, 2008; Hofmann & Asmundson, 2008; Teasdale et al., 1995; Way et al., in press). However, both attention and emotion regulation depend on the more basic prefrontal cortex function of wakefulness, which is currently under-researched in the meditation field. In order to *thoroughly* explore practice-specific mechanisms of action, I aim to investigate the effects of the two components of mindfulness training (FA and OM) on *all three* indices of PFC functioning: 1) attention, 2) emotional regulation *and* 3) wakefulness.

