wakefulness or sleep propensity. However, attention and emotion regulation are dependent on adequate wakefulness and compromised when wakefulness is low or sleep propensity is high (Banks & Dinges, 2007; Chuah et al., 2006; Couyoumdjian et al., 2009; Dinges et al., 1997; Drummond et al., 1999; Franzen et al., 2008; Goel et al., 2009; Harrison & Horne, 1998; Harrison et al., 2000; Ingre et al., 2006; Lim & Dinges, 2008; Lim et al., 2009; Nilsson et al., 2005; Thase et al., 1997; Van Dongen et al., 2003; Walker, 2009; West et al., 2009; Yoo, Gujar et al., 2007; Yoo, Hu et al., 2007; Zohar et al., 2005). Therefore knowledge of practice-specific effects on wakefulness will provide foundational information for understanding mechanisms of action. In order to provide the most comprehensive understanding of mechanism of action, this study will investigate all 3 domains of PFC functioning: Attention, emotion reactivity/regulation, and wakefulness.

***B4: If successful, this trial will provide:*** (a) The first, separate manualized treatment modules for the two core components of mindfulness with precise criteria for FA and OM meditation practices, (b) information about the clinical efficacy of each component/practice alone and in contrast to the standard combined treatment package and (c) information about the specific mechanisms of action for each component/practice. This information will identify *which* practices are most beneficial and *why* they are effective.

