### **4.2 Secondary Objectives**

•**Aim 4:** To assess and compare the effects of FA, OM and MBCT on subjective and objective measures of 3 domains of PFC functioning:

| PFC Domain               | Objective                  | Self-report |
|---------------------------------|-----------------------------------|--------------------|
| attention                       | SART                              | FFMQ, MAAS         |
| emotional reactivity/regulation | ERRT                              | DERS, SCO          |
| wakefulness                     | 5-9 HZ EEG power
sleep latency | KSS                |

•**Aim 5:** To determine which neurobehavioral processes (attention, emotion regulation, wakefulness) drive the clinical benefits of mindfulness training, independent of treatment allocation or practice type.

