#### **11.3.3.2 To determine which neurobehavioral process drives the clinical benefits of mindfulness:**

I chose multiple regression because it can evaluate associations between clinical outcome and multiple correlated continuous and categorical variables (it also fits my training goal of increasing multivariate statistical knowledge). Multiple regression analyses will be conducted across all groups to maximize power and allow for between-treatment comparisons. Criterion variables will include clinical outcome measures of affective disturbance and wellbeing (IDS, DASS, PANAS, WBS) (baseline- 3 month follow-up change scores). Aggregate scores for 1) attention, 2) emotional reactivity/regulation and 3) wakefulness will be entered as separate predictors. Variables that are not equivalent at baseline but may impact outcomes (e.g. sex, education etc) will also be entered as predictor variables. Hypothesized interactions between wakefulness, attention and emotion regulation will be also evaluated using multiple regression.

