##### **11.4.4 Basic Calculations**

While effect sizes in mood and sleep following mindfulness training are large, the differences between active treatments tend to be small (Wampold et al., 1997). A sample size of 90 (30 per intervention) will be able detect a small effect size ( $d=.33$ , power  $>.80$ ,  $\alpha=.05$ ).

**Method of calculation: G\*power 3.1.3****F tests - ANOVA:** Repeated measures, within-between interaction

**Analysis:** A priori: Compute required sample size  
 $\alpha$  err prob = 0.05  
Power (1- $\beta$  err prob) = 0.80  
Number of groups = 3  
Number of measurements = 2  
Nonsphericity correction  $\epsilon$  = 1

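### Aim 5's joint regression estimates only the direct effect of wakefulness, so a null coefficient there cannot rule wakefulness out as a driver of benefit

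*Protocol*

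**What the plan says.** The protocol gives wakefulness a place upstream of the other two processes. Section 2.2 says that "both attention and emotion regulation depend on the more basic prefrontal cortex function of wakefulness". The B3 paragraph of the Innovation text in section 3 calls wakefulness foundational and adds that "attention and emotion regulation are dependent on adequate wakefulness and compromised when wakefulness is low or sleep propensity is high".

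Section 4.2 gives Aim 5: "To determine which neurobehavioral processes (attention, emotion regulation, wakefulness) drive the clinical benefits of mindfulness training, independent of treatment allocation or practice type".

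Section 11.3.3.2 gives the analysis. "Multiple regression analyses will be conducted across all groups to maximize power and allow for between-treatment comparisons", with baseline to 3-month change in IDS, DASS, PANAS and WBS as criterion variables. "Aggregate scores for 1) attention, 2) emotional reactivity/regulation and 3) wakefulness will be entered as separate predictors". The method is chosen because "it can evaluate associations between clinical outcome and multiple correlated continuous and categorical variables". The only stated handling of links among the three processes is this: "Hypothesized interactions between wakefulness, attention and emotion regulation will be also evaluated using multiple regression".

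No model relates wakefulness to clinical outcome without the other two processes. Section 11.3.3.1 compares treatments on each process measure and does not link wakefulness to mood.

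**The concern.** If wakefulness feeds attention and emotion regulation, a regression holding those two fixed removes the part of its effect that runs through them. What remains is the direct effect. Under the same ordering, the attention and regulation coefficients are adjusted for wakefulness as their common cause. The three coefficients then answer different questions, and ranking them cannot name the driver.

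At stake is how a null wakefulness coefficient is read. The B3 paragraph presents wakefulness as an innovation of the study, and section 2.2 says the findings will be pilot data for a definitive test of mechanisms. A reader could drop wakefulness from that later trial on the strength of a coefficient that was never able to show its full effect.

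**Working it through.** **The plan's own figure.** Section 11.4.4 states "A sample size of 90 (30 per intervention) will be able detect a small effect size"; the output gives d = .335. For the 3-group, 2-time interaction F test with f = d/2 = .1675 and a within-person correlation of 0.5 (assumed, not stated), λ = f²·N·m/(1−ρ) = .1675² × 90 × 2 / 0.5 = 10.1 on 2 and 87 df. Power is 0.805 and the minimum N is 89, so the figure reproduces. It does not bear on Aim 5, for which no power figure is given. I take only n = 90 and α = .05 from it.

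**Joint or separate entry?** The words about separate predictors could, alone, mean three regressions. The choice of a method for correlated variables, and the interactions among the three, make joint entry the natural reading.

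**Algebra.** Write W for wakefulness, A for attention, E for emotion regulation and Y for outcome, all standardised:

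- A = aW + error, E = aW + error
- Y = bA + bE + cW + error

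The coefficient of W with A and E in the model is c. Without them it is c + 2ab. The joint model therefore leaves out 2ab. With c = 0 the joint coefficient is zero for any a and b.

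**Size.** The path values are assumptions, since the protocol gives none: b = 0.3, error-free scores, n = 90, 4,000 simulated trials per setting. Flagged means p < .05.

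| a | c | Total c + 2ab | Joint W coefficient | W flagged, joint | W flagged, without A and E | A flagged, joint |
|---|---|---|---|---|---|---|
| 0.3 | 0 | 0.18 | 0.00 | 5% | 41% | 82% |
| 0.5 | 0 | 0.30 | 0.00 | 5% | 83% | 76% |
| 0.7 | 0 | 0.42 | 0.00 | 5% | 99% | 63% |
| 0.3 | 0.1 | 0.28 | 0.10 | 15% | 76% | 86% |
| 0.5 | 0.1 | 0.40 | 0.10 | 14% | 98% | 81% |
| 0.7 | 0.1 | 0.52 | 0.10 | 11% | >99% | 70% |

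With c = 0.2 the joint model flags W in 32 to 53% of trials, against 96 to 100% without A and E.

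**Ranking.** Take a = 0.5, c = 0.1. The total effect of W is 0.1 + 2 × 0.5 × 0.3 = 0.40, above the 0.30 of either other process. The joint coefficients are 0.10, 0.30 and 0.30, so W ranks last.

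**Interactions.** Adding the three pairwise products with c = 0 leaves the W coefficient at 0.00, flagged in about 5% of trials. An interaction tests whether one process changes the effect of another; it does not recover the path through them.

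**Measurement error.** With c = 0, a = 0.4 to 0.6, and reliability of the A and E scores of 0.5 to 0.8 (assumed), the joint W coefficient is 0.06 to 0.22 against a total of 0.24 to 0.36, and W is flagged in 8 to 47% of trials. The loss is smaller but remains.

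**If the ordering is wrong.** Let W have no effect on anything, with paths of 0.3 from A and E to outcome. If one shared cause moves all three processes (loadings 0.4 to 0.7, assumed), the regression without A and E flags W in 14 to 81% of trials. If A and E drive W (paths 0.4 to 0.6, assumed), it flags W in 63 to 94%. The joint model flags W in about 5% in both cases.

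**The case against.** The strongest reply has four parts.

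- **Premise.** Dependence on adequate wakefulness could mean an enabling or threshold condition rather than a linear path, and interactions are a fair test of that. The protocol never says that wakefulness acts only through the other two; section 3.1 says it is unknown which process matters most. This stands against any claim that the coefficient will be zero. It does not rescue a null coefficient as evidence of no effect.
- **Text.** Section 11.3.3.2 speaks of analyses in the plural, does not fix the order of entry, and gives no rule that coefficients will be ranked. This also stands. A reader might infer that the plan commits to one regression and to naming a driver from it; the wording does not go that far. But no model in the section is described as giving the total effect of wakefulness.
- **Validity.** The joint model answers a proper question. If wakefulness works wholly through the other two, naming those as the proximal drivers is correct. This stands, and it means that the coefficients need labels, not that the model is wrong.
- **Remedy.** One might infer that the joint model should be replaced, with the total effect of wakefulness ranked against the adjusted effects of the other two. The documents do not support that. Sections 5.2 and 9.7 place the laboratory measures of all three processes at the same pre- and post-treatment visits, so the data cannot confirm their order. The last check above shows how often a wakefulness-only model could credit an inert process.

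Aim 5 is also a secondary objective in a pilot that sections 11.1 and 11.4.1 direct at estimation rather than significance. That limits the weight of the point, but a mislabelled estimate misleads as readily as a mislabelled test.

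**Conclusion.** The point holds in a limited form. If the ordering in section 2.2 and the B3 paragraph is right and the three scores are entered jointly, the wakefulness coefficient is a direct effect. It is zero under full mediation, attenuated relative to the total effect under partial mediation, and less attenuated when attention and regulation are measured with error. A null joint coefficient therefore cannot show that wakefulness does not drive benefit, and the three coefficients should not be ranked to name the driver.

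The algebra needs only linearity and the stated ordering. The percentages rest on assumed paths and, in the table, on error-free scores, so they illustrate the problem rather than predict this trial. It does not follow that the joint model is invalid or that the analysis will dismiss wakefulness.

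**What to change.** In section 11.3.3.2:

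1. Keep the joint model, and say explicitly that the three scores are entered together.
2. Add, for each outcome, a regression with wakefulness and the same covariates, including treatment arm in both models, but without attention and emotion regulation.
3. Report both wakefulness coefficients: the added one as the total effect, conditional on the ordering in section 2.2, and the joint one as the direct effect.
4. State that a null direct effect does not rule out wakefulness as a driver, and that the three joint coefficients will not be ranked for that purpose.
5. Report the difference between the two wakefulness coefficients with a bootstrap interval, as exploratory, because measures from the same visits cannot confirm the order.

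The cost is wording and one extra regression per outcome on data already to be collected, with no new participants or measurements. The drawback is that the total effect may be confounded if the ordering is wrong, which is why the joint model is retained.
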